## Abstract

**Background:**

Currently 1 in 11 women over the age of 60 in Australia are diagnosed with breast cancer. Following treatment, most breast cancer patients are left with shoulder and arm impairments which can impact significantly on quality of life and interfere substantially with activities of daily living. The primary aim of the proposed study is to determine whether upper limb impairments can be prevented by undertaking an exercise program of prolonged stretching and resistance training, commencing soon after surgery.

**Methods/design:**

We will recruit 180 women who have had surgery for early stage breast cancer to a multicenter single-blind randomized controlled trial. At 4 weeks post surgery, women will be randomly assigned to either an exercise group or a usual care (control) group. Women allocated to the exercise group will perform exercises daily, and will be supervised once a week for 8 weeks. At the end of the 8 weeks, women will be given a home-based training program to continue indefinitely. Women in the usual care group will receive the same care as is now typically provided, i.e. a visit by the physiotherapist and occupational therapist while an inpatient, and receipt of pamphlets. All subjects will be assessed at baseline, 8 weeks, and 6 months later. The primary measure is arm symptoms, derived from a breast cancer specific questionnaire (BR23). In addition, range of motion, strength, swelling, pain and quality of life will be assessed.

**Discussion:**

This study will determine whether exercise commencing soon after surgery can prevent secondary problems associated with treatment of breast cancer, and will thus provide the basis for successful rehabilitation and reduction in ongoing problems and health care use. Additionally, it will identify whether strengthening exercises reduce the incidence of arm swelling.

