We therefore aim to conduct a randomized controlled trial to determine whether an intensive exercise program, commencing 4 weeks after breast cancer surgery, prevents weakness, pain, swelling, and loss of range in the upper limb. We will also determine whether quality of life (as measured by arm symptoms) improves for women who undertake an intensive exercise program early after breast cancer surgery. Lastly, we will determine the effect of resistance training soon after surgery on the short-term occurrence of lymphedema.

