### Interventions

#### Usual care

Women will receive the same care as is now provided in the three participating hospitals. Women are typically admitted on the day of surgery and are discharged 2 to 7 days after surgery. While in hospital, they are seen by a physiotherapist who reviews gentle shoulder exercises which are outlined in a pamphlet. The active assisted shoulder exercises are for shoulder protraction, elevation and abduction. In addition, women are seen by an occupational therapist who discusses issues related to prevention of lymphedema. Women are not followed by either the physiotherapist or the occupational therapist after discharge from the hospital.

Women in the Usual Care group will not be given a home program of exercises, apart from those described in the pamphlet. To control for attention from the research assistant, they will meet with the research assistant fortnightly at which time their arm will be assessed with multifrequency bioimpedance analysis [15] for the development of lymphedema, but no specific advice will be given about exercise and management.

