#### Exercise group

Commencing Week 4 following surgery, women will attend 8 weekly exercise sessions comprising stretching exercises and resistance training, and will commence a daily home program of similar exercises. We have used these exercises in our pilot study [10], and they are well tolerated.

Each week, there will be a supervised weekly session at which women will perform the shoulder exercises targeting the muscles and shoulder movements likely to be at risk. Stretches will consist of prolonged holds of at least 5 minutes duration. The stretches are performed in supine and are undertaken for the shoulder extensors, and for pectoralis major and minor muscles. For women unable to achieve >90 deg forward flexion, shoulder extension and abduction stretches will be performed whilst seated. For both stretches, the arm will be elevated in the appropriate direction and supported on pillows; the aim of these stretches is to provide a comfortable stretch in the region of the participant's axilla. Each of these stretches will also be held initially for 5 minutes and progressed up to 20 min. Once shoulder flexion >90 deg is achieved, the participant will undertake the stretches in supine. The muscles targeted for resistance training include the shoulder flexors, abductors, external rotators and horizontal flexors. For strength training, the resistance will be determined by the Borg Effort Scale [16] and provided by free weights. Each week, the exercises will be monitored, and progressed as required.

In addition to the weekly supervised sessions, women will perform a daily home program. The program will consist of i) a daily stretching program and ii) a strengthening program undertaken on alternate days. The stretching program will be the same as that undertaken at the weekly supervised session. For the strengthening program, the same muscles will be trained as in the weekly supervised sessions but rather than free weights, the resistance will be provided by theraband. Participants will be instructed to perform two sets of 8 – 12 repetitions for each exercise. Participants will be instructed to work at a target of 15 ('Hard') on the Borg Effort Scale [16]

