#### Statistical analysis

Treatment group will be coded to enable blinded analysis, which will be by "intention-to-treat". For the primary outcome measure, the change from baseline score for arm symptoms on the operated side derived from the BR23 will be determined. The mean change will be compared between the two groups using Student's two-sample t-test.

Our secondary analyses will examine the effect of adjusting for the stratifying factor (type of surgery) or any important prognostic factors that show a clinically important imbalance between groups. This will be done using multiple linear regression, with the baseline arm symptoms score as a covariate and the final arm symptoms score as the outcome variable.

For measures of strength, range of motion, and lymphedema, the difference between the operated and non-operated side will be determined. These differences at 6 months will be compared using a two-sample t-test or distribution-free equivalent, as appropriate. For other aspects of the quality of life score, the mean changes from baseline will be compared between the two groups using Student's two-sample t-test. As for the primary outcome, multiple regression analyses will be used for all secondary variables to adjust for covariates, including baseline differences.

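### The lymphedema aim is worded as an effect of resistance training, but the two-arm design can only estimate the effect of the combined stretching and resistance programme

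*Protocol article*

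**What the plan says.** Two statements in the protocol article promise a result for one component of the intervention. The Discussion paragraph of the abstract says of the study that "it will identify whether strengthening exercises reduce the incidence of arm swelling". The last sentence of the Background says "we will determine the effect of resistance training soon after surgery on the short-term occurrence of lymphedema".

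The design is described as follows.

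- **Arms** (abstract, Methods/design): "women will be randomly assigned to either an exercise group or a usual care (control) group".
- **Exercise arm, supervised** (Interventions, Exercise group): "women will attend 8 weekly exercise sessions comprising stretching exercises and resistance training".
- **Exercise arm, at home** (same section): "i) a daily stretching program and ii) a strengthening program undertaken on alternate days".
- **Control arm** (Interventions, Usual care): "Women in the Usual Care group will not be given a home program of exercises, apart from those described in the pamphlet". These women also meet the research assistant fortnightly for a bioimpedance assessment.
- **Analysis** (Statistical analysis): for strength, range of motion and lymphedema, the difference between operated and non-operated side is formed, and "These differences at 6 months will be compared using a two-sample t-test or distribution-free equivalent, as appropriate". Multiple regression is added to adjust for covariates.

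Elsewhere the article words the effect correctly. The primary aim in the abstract and the closing claim in the main Discussion both refer to a programme of resistance training and prolonged stretching together.

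**The concern.** Both statements name resistance training as the cause of any difference in lymphedema, yet every woman allocated to resistance training is also allocated to prolonged stretching, and no control woman is given that stretching programme. A difference between arms could come from either component, from the two together, or in part from the different amount and kind of contact.

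The Background reports a common belief that vigorous arm exercise induces lymphedema and presents early resistance training as untested. A finding labelled as the effect of resistance training would be taken as an answer to that question, in either direction, and could be applied to resistance exercise given without stretching. The trial would not support that use.

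**Working it through.** **1. What the sample size is built for.** Inputs from Sample size calculations: difference 12 points, standard deviation 25, two-sided 5%, power 80%, loss 20%, 90 women per arm.

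- Normal approximation: n = 2 × (1.96 + 0.84)² × 25² / 12², which rounds up to 69 per arm.
- Two-sample t-test, the planned test: 69.1, so 70 per arm evaluable. Allowing for loss, 70 / 0.8 = 87.5, so 88 per arm.
- With 90 × 0.8 = 72 evaluable per arm, t-test power is 81.6%.

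The stated 180 women is therefore consistent with its inputs. It is sized for a single contrast, programme against usual care, on arm symptoms. This does not bear on the point in question, except to confirm that the plan has one contrast and two groups.

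**2. What that contrast estimates for lymphedema.** Write R for the effect of resistance training, S for stretching, I for their interaction and C for the difference in contact (weekly supervised sessions against fortnightly meetings). The difference between arms is

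Δ = R + S + I + C, so R = Δ − S − I − C.

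The trial estimates Δ. No arm receives stretching alone or resistance alone, so S, I and C are not estimated separately. Taking I = C = 0 for simplicity:

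| Assumed S | Implied R |
|---|---|
| S = 0 | R = Δ |
| S = Δ | R = 0 |
| S = −R | Δ = 0, whatever the value of R |

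The same observed Δ fits all values of R, depending on an S the trial does not measure. More women would narrow the interval around Δ and leave this unchanged. The last row is a logical possibility; nothing in the article suggests that it is likely.

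**3. Whether the planned analysis helps.** The two-sample comparison estimates Δ. Regression on baseline covariates gives an adjusted Δ. Neither separates R from S, because both components are assigned by the same allocation. The compliance diary could support an analysis by exercise actually performed, but that would be a non-randomised comparison, and the article describes none.

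**4. Whether the wording might be shorthand.** The Background attaches its first two aims to an intensive exercise programme, one of them already covering swelling, and then names resistance training in a separate final sentence. The abstract makes the same shift, from exercise in general to strengthening in an added sentence. Earlier in the Background each component has its own rationale: resistance for lymphedema and weakness, stretching for range and stiffness. The resistance-specific aim follows from that division, so its literal reading is the natural one.

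**The case against.** The best reply is that this is loose wording in two sentences of an otherwise well-framed article. The primary aim, the stated design purpose and the main Discussion all refer to the programme, and the Background already has a programme-level aim that includes swelling. The article also explains why resistance is named: it links resistance work to lymphedema and stretching to range and stiffness, and nowhere suggests that stretching affects swelling. On contact, the fortnightly visits in the usual care arm are there to control for attention, and lymphedema is measured by bioimpedance and limb circumference by an assessor stated to be blinded, so an attention effect is less likely here than on a self-reported outcome.

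Much of this is fair. Testing a combined programme is a legitimate choice, and the contact difference is the weakest of the rival explanations. The core point stands all the same. That stretching has no effect on lymphedema is an assumption the article does not state, and if it is relied on, the result depends on it and not on randomisation. That other sections are worded correctly shows that the two sentences are out of line with them; it does not make those sentences accurate.

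**Conclusion.** The concern holds. As written, the abstract and the last sentence of the Background state an aim that the design cannot meet. This is a matter of identification, so no number measures it: the resistance effect cannot be recovered from the randomised comparison at any sample size. The conclusion rests only on the two-arm structure and on both exercise components being given to the same arm, which the article states plainly. It does not rest on any belief that stretching, supervision or monitoring actually changes lymphedema.

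The problem is confined to this additional lymphedema aim. The primary outcome, the primary comparison and the sample size are untouched. It should still be corrected, because it governs what the trial may claim on a safety question that the article presents as open.

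**What to change.** In the last sentence of the Background and in the Discussion paragraph of the abstract, replace the reference to resistance training or strengthening exercises with the effect of a combined stretching and resistance exercise programme on the short-term occurrence of lymphedema. Add a sentence saying that no conclusion will be drawn for either component alone. Since the Background already has a programme-level aim on swelling, the reworded sentence could be merged with it. The cost is wording only, and the price is a narrower claim.

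Keeping the resistance-specific aim would need a different trial: a further arm so that one comparison differs only in resistance training, or a 2×2 factorial design. A third arm of the present size would bring the total to 3 × 90 = 270 women, but 90 per arm was derived for arm symptoms. The article gives no lymphedema incidence from which to size that comparison. Rewording is the proportionate change.

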**Trial Registration:**

The protocol for this study is registered with the Australian Clinical Trials Registry (ACTRN012606000050550).

## Background

Upper limb arm morbidity resulting from treatment for early breast cancer is a common sequela of treatment for breast cancer [1]. In a study of 644 older women treated for breast cancer, 54% reported a decline in upper body function compared to 10% in the control group who had not undergone treatment [2]. Based on reports of upper limb morbidity [2], current practices do not adequately address or prevent the impairments that may arise from management of the tumour. While the long-term morbidity is well documented, little evidence is available to inform clinicians in the best way to minimise and prevent these upper limb problems. As upper limb morbidity is associated with reduced quality of life [3,4], particularly emotional, social and physical functioning aspects, as well as body image and lifestyle [5], it is important that effective preventive strategies be identified.

The potential benefits of progressive resistance training soon after surgery has not been investigated even though many women report shoulder weakness [4,6-8]. It is commonly believed that vigorous arm exercises will induce lymphedema [9] although evidence from our pilot study challenges this belief [10]. To date, no studies have investigated the use of resistance training early after surgery, although this may be the stage at which exercises have the greatest effect in preventing lymphedema and muscle weakness.

Stretching is advocated following breast cancer surgery; however, given the reports of reduced range and consequent shoulder stiffness [4,6-8,11], the stretching protocols do not appear to have been performed in a particularly effective way. Little detail of the actual exercises has been provided in the available randomized controlled trials [12]. In several studies, participants were seen by a physiotherapist but details of the exercises, including duration, were omitted [12]. Evidence from animal models suggests that adverse physiological adaptations can be prevented with prolonged daily stretching [13] and prolonged stretches at the shoulder have been shown to be highly effective in other patient populations at risk of developing significant loss of range [14]. Thus, prolonged stretches may decrease the loss of range and joint stiffness consequent to treatment for breast cancer.

We therefore aim to conduct a randomized controlled trial to determine whether an intensive exercise program, commencing 4 weeks after breast cancer surgery, prevents weakness, pain, swelling, and loss of range in the upper limb. We will also determine whether quality of life (as measured by arm symptoms) improves for women who undertake an intensive exercise program early after breast cancer surgery. Lastly, we will determine the effect of resistance training soon after surgery on the short-term occurrence of lymphedema.

## Methods/design

### Design

To determine the efficacy of an intensive upper limb exercise program for women soon after breast cancer surgery, we will conduct a multi-center, single-blind randomised controlled trial. Women will be recruited from 3 large hospitals with breast cancer oncology services in Sydney, Australia. Breast Cancer Nurses will inform potential participants about the study when they visit the patient after surgery. To provide sufficient time for the wound to heal, women will enter the study 4 weeks after surgery.

A record will be kept of the number of invitations to participate, the number of potential participants who volunteer to participate, and the number of screened patients who are ineligible and the reason for their ineligibility.

Ethical approval has been received from the participating hospitals as well as from The University of Sydney. All participants will provide written informed consent.

### Participants

Women will be included in the study if they: have undergone a breast cancer intervention that included surgery to the axilla; can attend for treatment and follow-up; understand English and consent to participate and be randomised to either treatment group. Women scheduled for adjunct treatments including radiotherapy, chemotherapy and breast reconstruction will be included.

Women will be excluded if they have not had surgery to the axilla or have undergone bilateral operations, present with infection at the baseline measurement or have received previous treatment for breast cancer or have metastatic disease. In addition, women will be excluded if they have sustained a fracture, undergone surgery in the upper limbs, or suffered any neurological deficit or other injury to either upper limb that may interfere with the test procedures. Lastly, women will be excluded if they undergo breast reconstruction and as a consequence, their specialist has indicated that they are not to participate.

### Randomization

An investigator who has no direct contact with the subjects will be responsible for generating the randomisation list. Randomisation will be stratified by whether women receive axillary node resection or sentinel node biopsy. The randomisation list will be used to prepare numbered opaque envelopes with the group allocation sealed inside by a person not involved in the study. Immediately after baseline assessment, women will be randomly allocated to either the usual care or exercise group. The protocol for this study is registered with the Australian Clinical Trials Registry (ACTRN012606000050550).

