### Measurement

All measurements will be undertaken by a research assistant blinded to the group to which women were allocated. Variables will be measured before randomization, at 8 weeks (the end of the intervention phase) and then at 6 months to determine the effect of the intervention on physical and psychosocial outcomes. In addition, information about the breast cancer treatment regimen, pathology report, age, weight, and previous shoulder pathology will be obtained from the patient's medical record at the baseline assessment. Occurrence of side-effects and adverse events will be evaluated at each measurement occasion.

The primary outcome measure for treatment efficacy is arm symptoms on the operated side, derived from 3 items of the Breast Module (BR23). The BR23 is a 23-item survey specific to women with breast cancer. The 3 selected items ask whether in the past week the woman has had pain in her arm or shoulder, a swollen arm or hand, and whether it was difficult to raise or move her arm sideways. For each question, there are 4 possible responses, ranging from 'not at all' to 'very much'. The raw scores for these questions are summed and then subjected to linear transformation to provide an overall score, with a maximum of 100. A high score indicates a high level of symptoms. The primary endpoint for the trial is change in primary outcome from baseline to 6 months.

Secondary outcomes include other aspects of quality of life and measures of physical impairment.

Quality of life will be measured using the European Organisation for Research and Treatment of Cancer Quality of Life Questionnaire Version 3 (QLQ-C30) and the Breast Module (BR23). These surveys are specific to cancer patients and comprise a global health status/quality of life scale, as well as functional and symptom scales. These questionnaires are reliable, valid and sensitive to change and able to distinguish patients in different disease stages and with different performance status [17-19].

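### Hospital is neither a randomisation stratum nor a stated analysis term in this three-hospital trial: a modest, avoidable loss of precision in the treatment comparison

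*Protocol article*

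**What the plan says.** The Design section of the Protocol article makes this a multicentre trial: "Women will be recruited from 3 large hospitals with breast cancer oncology services in Sydney, Australia".

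The Randomization section gives one stratifying factor: "Randomisation will be stratified by whether women receive axillary node resection or sentinel node biopsy". Allocation is by numbered opaque envelopes straight after the baseline assessment. The section does not say whether one series serves all hospitals or each hospital holds its own.

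The Measurement section defines the target: "The primary endpoint for the trial is change in primary outcome from baseline to 6 months". The Statistical analysis section gives the primary test: "The mean change will be compared between the two groups using Student's two-sample t-test". Its secondary analyses "examine the effect of adjusting for the stratifying factor (type of surgery") or for important prognostic factors that turn out to be clinically imbalanced. The stratifying factor is named in the singular, and hospital is not mentioned.

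On the comparator, the Usual care section says "Women will receive the same care as is now provided in the three participating hospitals". It then describes a single pattern of inpatient care for all three.

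**The concern.** Hospital is known for every woman before she is randomised. It can stand in for things that act after baseline, such as local patterns of adjuvant treatment, although the article does not say that these differ by site. Where hospital plays no part in allocation or analysis, one of two things follows:

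- **One shared envelope series per surgery type.** Nothing balances the arms within a hospital. An uneven split combines with any hospital difference in outcome to move the treatment estimate by chance.
- **Separate envelope sets at each hospital.** Hospital is then an unstated stratifier that the t-test ignores, and the standard error is somewhat too large.

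In both cases, between-hospital variation sits in the error term when it could be removed. At stake is the precision of the primary comparison, which is powered for a 12-point difference.

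**Working it through.** **Inputs from the article (Sample size calculations).** 90 women per group, a 12-point difference, SD 25, two-sided 5%, 80% power and 20% loss. Evaluable women per group: 90 × 0.8 = 72.

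**Assumptions, because the article gives no figure.** 60 women recruited per hospital. A between-hospital SD, s, of 3, 5 or 8 points in the change in arm symptoms. 25 is taken as the total SD of the analysed change, hospital variation included.

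**1. The plan's own figure.** By the normal approximation, n per group = 2 × (1.960 + 0.842)² × 25² / 12² = 68.1, so 69. The exact t calculation gives 70. Allowing for loss, 70 / 0.8 = 87.5, so 88 per group and 176 in total, close to the stated 180. With 72 per group, exact-t power is 81.6%. The sample size stands.

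**2. Chance of an uneven split.** With arm totals fixed at 90:90 and no balancing by hospital, the number of a hospital's 60 women allocated to exercise is hypergeometric (180 women, 90 allocated, 60 drawn). Stratification by surgery type is ignored here.

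- 36:24 or worse in a given hospital: 2 × P(X ≥ 36) = 8.2%.
- 36:24 or worse in at least one of the three: about 19%.
- 40:20 or worse in a given hospital: 0.25%.
- For comparison, 36:24 or worse under independent coin-toss allocation, Bin(60, 0.5): 15.5%. That model does not hold the groups at 90 each.

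**3. Shift of the estimate through hospital imbalance.** SD of the shift = s × √(2/72) = s / 6.

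**4. Gain from a hospital term.** Share of variance = s² / 625. Within-hospital SD = √(625 − s²). SE = within-hospital SD × √(2/72). Power is from the noncentral t with two degrees of freedom fewer.

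| Hospital SD s (assumed) | Share of variance | SD of chance shift | SE of difference | Power |
|---|---|---|---|---|
| No hospital term | – | – | 4.17 | 81.6% |
| 3 | 1.4% | 0.5 points | 4.14 | 82.1% |
| 5 | 4.0% | 0.8 points | 4.08 | 83.1% |
| 8 | 10.2% | 1.3 points | 3.95 | 85.5% |

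**5. Validity of the planned test.** Trials were simulated with 72 women per group, three equal hospitals and a hospital variance share of 1%, 5% or 10%, with 8,000 runs per setting. The unadjusted t-test had a type I error of 4.9% to 5.1%. Its power was about 82%, against 82% to 85% with a hospital term.

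**The case against.** The strongest reply is that hospital matters little here, and much of it stands.

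- **Care is not shown to differ.** A reader might infer from the Usual care section that each hospital delivers its own care. The article does not support that. It describes one pattern of physiotherapist visit, pamphlet and occupational therapist visit. The discharge range of 2 to 7 days is not broken down by hospital.
- **That care comes before randomisation.** The same section says "Women are not followed by either the physiotherapist or the occupational therapist after discharge from the hospital", and the Design section says "women will enter the study 4 weeks after surgery". Both arms have had the inpatient care by then. The primary endpoint is a change from baseline, so stable hospital differences in level largely cancel and only differences in change remain. This protection is weaker for strength, range of motion and lymphedema, where the first-line test compares side-to-side differences at 6 months without subtracting baseline.
- **There is no confounding in the sense of bias.** A reader might infer that an uneven split confounds hospital with treatment. Under randomisation this is chance error, which the standard error already reflects. With hospital-held envelopes the t-test is, if anything, conservative.
- **The plan already permits adjustment.** Hospital could qualify as an imbalanced prognostic factor. But that clause covers secondary analyses only and depends on imbalance seen in the data, so it is not a prespecified term.
- **The article is condensed.** A fuller plan, not shown, might add a hospital covariate. The stratification and the primary test, however, are both stated here, and hospital is in neither. Its absence is therefore a stated choice open to comment, and an analysis plan cannot add a stratum to an allocation already made.

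**Conclusion.** The point holds as a minor design weakness. Hospital is missing from both the stated stratification and the stated analyses, and the cost is avoidable noise. Over the assumed range of hospital SDs, that noise has an SD of 0.5 to 1.3 points against a 12-point target, and a hospital term would gain roughly 0.5 to 4 percentage points of power. The planned 80% power is met with or without the term, the sample size is unaffected, and the type I error is sound. The size rests on assumed hospital SDs and equal recruitment. If hospitals hardly differ in change, the gain is close to nil. The case for acting is that the remedy is cheap and uses information already held for every woman.

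**What to change.** **Before recruitment opens.** Prepare a separate numbered envelope series for each combination of hospital and axillary-surgery type, 3 × 2 = 6 series, in permuted blocks of concealed, varying size.

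**Analysis.** Replace the primary t-test with a prespecified regression of the 6-month arm symptoms score on treatment, baseline score, surgery type and hospital (two indicator terms). Use the same hospital and surgery terms in the secondary regressions. The primary model has to change too: stratifying by hospital while keeping the unadjusted t-test would leave the new stratifier ignored in the main comparison.

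**If recruitment has begun.** Leave the allocation list as it is and make only the analysis change, including in the primary model, before the data are unblinded.

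**Cost.** Four more envelope series than the two that surgery type alone requires, a short change to the analysis text, and four degrees of freedom (two for hospital, one each for surgery type and baseline) out of the t-test's 142 with 144 evaluable women. No extra data are needed.
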